**Figure 1 F1:**
[figure not shown]
**Summary of study timeline**. Following baseline investigations, 50 patients will be randomised to recieve 200 mg of perhexiline or matched placebo for one month. At one month all baseline tests will be repeated and a subgroup will undergo cardiac catheterisation.

Baseline tests will be repeated in full after completing one month of treatment with perhexiline or placebo. A willing subgroup of patients will undergo right and left heart catheterisation for invasive haemodynamic measurements and cross heart sampling. Those subjects taking part in the invasive subgroup will also undergo cardiac magnetic resonance imaging (CMR) for accurate estimation of left ventricular cardiac mass.

Female subjects of child-bearing potential will be excluded from the study.

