### Randomisation and Drug Monitoring

Following baseline investigations ensuring normal liver function tests, participants will be randomised by computer to commence with perhexiline 200 mg oral daily or an identical placebo for one month (Figure 1). Randomisation will be done in a 50:50 ratio of perhexiline:placebo in blocks of 10.

At one week duration, all patients will have a blood sample taken for serum perhexiline level with the researcher blinded to the subject's treatment allocation. This level will be evaluated by a doctor unblinded to the subject's treatment allocation. The dosage of perhexiline will be adjusted according to the accepted dosing protocol (Table 2). An equal number of dummy dose adjustments will be made to those patients on placebo to help to maintain blinding.

**Table 2 T2:** Perhexiline dose titration according to serum perhexiline level.

*Perhexiline concentration (mg/L)*	*Recommended new daily dose (mg)*
0.00-0.05	300
0.05-0.15	250
0.15-1.00	200
1.00-1.50	100
1.50-2.00	50
>2.00	Cease for 1 week and start 50 mg alternate days

At the end of one month of therapy, patients will undergo a repeat of baseline investigations and a further perhexiline level will be taken to ensure therapeutic levels were achieved and compliance maintained.

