### Planned Statistical Analysis

Comparisons will be performed between the groups at baseline and after the 4 week treatment. The normality of distribution of all continuous variables will be determined using a normality plot and the Kolmogorov-Smirnov test. Normally distributed variables will be analysed using unpaired t-tests, χ^2 ^or repeated measures analysis or variance. Variables not normally distributed will be log transformed prior to analysis to achieve normal distribution or, if this is not achieved, analysed by Mann-Whitney U or Kruskal-Wallis tests.

Analysis will be by intention-to-treat. A *p*-value of < 0.05 will be considered statistically significant.

Sample size calculations were based on the primary end point of change in PCr/ATP ratio after 4 weeks of treatment. Pilot work from our group using the same MRS technique and perhexiline revealed a 0.4 improvement in PCr/ATP ratio in the treatment group by comparing means. The response was normally distributed with a standard deviation of 0.5. Using this data, 26 subjects in each arm will provide at least 80% power of detecting a 0.4 change in PCr/ATP ratio using a two-tailed t-test at the 5% significance level. Recruiting 50 patients will allow for withdrawal, drop out or incomplete data.

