### Study Limitations

The study is powered for the primary endpoint (an increase in PCr/ATP ratio assessed after 4 weeks of treatment). It is accepted that the study is likely to be underpowered for the secondary endpoint of improvement in LV function. Nonetheless, a similar sized study using perhexiline in heart failure showed a dramatic, absolute increase in ejection fraction of 10% after 2 months of treatment[21]. This improvement had a standard deviation of approximately 10%. Assuming a similar distribution in this study, our sample size should allow us to detect an 8% improvement in ejection fraction, which is comparable to that demonstrated in a recent meta-analysis highlighting the effect of trimetazidine (another metabolic modulating agent) on ejection fraction in non-ischaemic heart failure[22].

No similar invasive work of this nature has been performed in human heart failure to allow an accurate power calculation for this component of the trial.

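### The plan requires 26 evaluable patients per arm (52) but randomises 50 and says that 50 covers losses, so there is no attrition allowance

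*Protocol article*

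**What the plan says.** The sample-size paragraph closes the Planned Statistical Analysis section of the protocol article. Its inputs come from pilot work that "revealed a 0.4 improvement in PCr/ATP ratio in the treatment group by comparing means". On variability it says: "The response was normally distributed with a standard deviation of 0.5". It concludes that "26 subjects in each arm will provide at least 80% power of detecting a 0.4 change in PCr/ATP ratio". The test it names is a two-sided t-test with alpha 0.05. The next sentence is the one at issue: "Recruiting 50 patients will allow for withdrawal, drop out or incomplete data".

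The rest of the article fixes 50 as the total over both arms. The Abstract and Study Design describe a trial of 50 subjects, and the Figure 1 legend says that "50 patients will be randomised to recieve 200 mg of perhexiline or matched placebo for one month". Under Randomisation and Drug Monitoring, "Randomisation will be done in a 50:50 ratio of perhexiline:placebo in blocks of 10", so 50 patients make five complete blocks with 25 in each arm. No expected loss rate is given anywhere. Study Limitations then states, without qualification, that the study is powered for the primary endpoint.

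**The concern.** Two adjacent sentences cannot both be true. If 26 per arm are needed for the stated power, 52 evaluable patients are needed, and recruiting 50 leaves the trial two short before anyone is lost. An allowance for losses requires a target above the evaluable number, not below it.

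The paragraph itself anticipates withdrawal, drop-out and incomplete data. The primary endpoint is the change in PCr/ATP over 4 weeks, so a patient needs usable spectra at baseline and at follow-up to contribute to it. Someone reading a null primary result would take from the current text that the trial kept at least 80% power after ordinary losses. The design does not have that property.

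**Working it through.** **Inputs** (all from Planned Statistical Analysis unless noted)
- Difference in PCr/ATP: 0.4
- SD: 0.5, so the standardised difference is 0.4 / 0.5 = 0.8
- Two-sided t-test, alpha 0.05
- 50 randomised in total (Abstract, Study Design, Figure 1 legend), allocated 1:1 (Randomisation and Drug Monitoring), so 25 per arm
- Loss rate: none stated. The evaluable numbers below 25 per arm are my assumptions, covering 4% to 20% loss.

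**Formula.** With n evaluable per arm, the noncentrality parameter is 0.8 × √(n/2) on 2n − 2 degrees of freedom. Power is the probability that a noncentral t with these parameters falls beyond the two-sided 5% critical value.

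**Step 1: reproduce the plan's figure.** At n = 26 the noncentrality is 0.8 × √13 = 2.884, with 50 degrees of freedom and critical value 2.009. Power is 80.7%. Solving for exactly 80% gives n = 25.5, so 26 is the smallest whole number that reaches it. The plan's 26 per arm is correct.

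**Step 2: rule out other readings.** If 26 were the total (13 per arm), power would be about 50%. A one-sample or paired t-test would need 15 patients, and a one-sided normal approximation would need 20 per arm. Of the calculations tried, only the two-sided two-sample t-test returns 26 per arm. The total is therefore 2 × 26 = 52.

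**Step 3: compare with the target.** 50 − 52 = −2, so the allowance for losses is negative.

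**Step 4: power and detectable difference with 50 randomised.** The detectable difference is the one that gives 80% power with SD 0.5.

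| Evaluable per arm | Loss from 50 (assumed) | Power for 0.4 | Difference detectable at 80% |
|---|---|---|---|
| 25 | none | 79.1% | 0.404 |
| 24 | 4% | 77.4% | 0.413 |
| 22.5 (average) | 10% | 74.6% | 0.427 |
| 22 | 12% | 73.6% | 0.432 |
| 20 | 20% | 69.3% | 0.455 |

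**Step 5: does the choice of formula matter?** The normal approximation gives n = 2 × (1.960 + 0.842)² × 0.5² / 0.4² = 24.5, rounded up to 25 per arm, with 80.7% power at 25. On that formula 50 patients meet the 80% target, but all 50 are used. At 24 per arm it gives 79.1%, below 80%. The allowance is therefore zero under the normal approximation and minus two under the t-test that the article names.

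**The case against.** The strongest reply is that the certain shortfall is negligible. With complete data the trial has 79.1% power against a promised 80%, and a routine normal approximation puts 25 per arm above 80%. The larger drops depend on loss rates that I chose. Treatment lasts only 4 weeks, and the article gives no basis for expecting 10% or 20% loss. The slip affects neither the type I error nor the estimate, and a confidence interval would show the precision achieved.

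Most of that stands, and it limits the point to the missing allowance. It does not rescue the sentence: the article itself expects some loss, and under neither formula does 50 leave room for any.

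Four stronger readings are tempting but not supported.
- *The trial is seriously underpowered.* This cannot be inferred. With complete data the gap is under one percentage point, and the size of any further gap depends on losses that the article does not quantify.
- *The ejection-fraction claim fails in the same way.* Study Limitations says that "our sample size should allow us to detect an 8% improvement in ejection fraction", with an SD of about 10%, which is again a standardised difference of 0.8. But that statement carries no power level, and the same section concedes that the study is likely to be underpowered for LV function. At 25 per arm the difference detectable at 80% power is 8.1 points, which rounds to 8.
- *The 0.4 is a within-arm change, so any rise on placebo would cut power much further.* The wording about the pilot result is ambiguous, the pilot data are not shown, and the article gives no figure for a placebo change.
- *Baseline adjustment would restore the power.* It might, but the gain depends on the baseline to follow-up correlation, which is not given, and on whether 0.5 is the SD of change or of follow-up values.

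**Conclusion.** The point holds as an internal contradiction on the primary endpoint. By its own correct calculation the plan needs 52 evaluable patients, yet it randomises 50 and presents that number as already covering losses. The absence of an attrition allowance is certain and does not depend on the formula.

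The effect on power is marginal if no one is lost (79.1% by the stated t-test, 80.7% by normal approximation). It becomes noticeable only with losses: about 75% power at 10% loss and 69% at 20%. These figures rest on the article's own difference, SD and test, on equal losses in the two arms, and on loss rates that I assumed.

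**What to change.** In Planned Statistical Analysis, keep 50 and delete the sentence claiming that it allows for losses. In its place, state what 50 randomised patients deliver for a difference of 0.4 with SD 0.5:
- about 79% power with complete data (detectable difference 0.404);
- about 74% with 22 evaluable per arm (0.432);
- about 69% with 20 evaluable per arm (0.455).

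Label the last two as illustrations unless an expected loss rate can be given. In Study Limitations, qualify the statement that the study is powered for the primary endpoint so that it refers to these figures. The ejection-fraction sentence needs no correction on this ground.

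The cost is wording only: no extra patients, no change to the analysis, and a slightly less favourable power statement. If the sponsor would rather have a genuine allowance, the alternative is to state a loss rate d and recruit 52 / (1 − d). For example, 52 / 0.90 = 57.8, so 58 patients at an assumed 10% loss. That costs 8 more patients than now planned.

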### Monitoring and Safety Assessments

When perhexiline levels are unmonitored, it has been associated with both hepatotoxicity and peripheral neuropathy. All patients will be screened both clinically and biochemically for any sign of these conditions. Perhexiline also lowers serum glucose levels. Patients who are diabetic will be made aware that the medication may cause hypoglycaemic and they will be instructed make frequent blood sugar measurements when starting the study. Perhexiline levels will be tested at one week and at the end of the study as outlined above.

All adverse events, including serious adverse events (SAEs), will be recorded and followed up for the duration of the study or until resolution. Assessment of adverse events will be performed by study investigators. All SAEs will be graded and reported to the sponsor. Any suspected unexpected serious adverse reactions will be reported to the sponsor, ethics committee and the Medicines and Healthcare Products Regulatory Agency. This study has been reviewed and approved by the South Birmingham Research Ethics Committee. Written informed consent will be obtained from all study participants.

### Study Limitations

The study is powered for the primary endpoint (an increase in PCr/ATP ratio assessed after 4 weeks of treatment). It is accepted that the study is likely to be underpowered for the secondary endpoint of improvement in LV function. Nonetheless, a similar sized study using perhexiline in heart failure showed a dramatic, absolute increase in ejection fraction of 10% after 2 months of treatment[21]. This improvement had a standard deviation of approximately 10%. Assuming a similar distribution in this study, our sample size should allow us to detect an 8% improvement in ejection fraction, which is comparable to that demonstrated in a recent meta-analysis highlighting the effect of trimetazidine (another metabolic modulating agent) on ejection fraction in non-ischaemic heart failure[22].

No similar invasive work of this nature has been performed in human heart failure to allow an accurate power calculation for this component of the trial.

## Discussion

The finding that perhexiline improves cardiac energetics by an increase in the PCr/ATP ratio would be an important contribution to support the future work of metabolic manipulation as a treatment for heart failure, even in the absence of coronary artery disease. PCr/ATP ratio has been shown to correlate with mortality, and an improvement in this index may also lead to an improved survival in this patient population.

Until now, the proposed mechanism of perhexiline is based on in vitro and animal work. By showing an increase in R/Q we can support the hypothesis of increased carbohydrate metabolism as a result of perhexiline therapy.

Improvement in mechanical efficiency would reveal that the above changes contribute, at least in part, to a direct improvement in cardiac function.

## List of Abbreviations

2,3-DPG: 2,3-diphosphoglycerate; AMARES: advanced method for accurate, robust and efficient spectral fitting; ATP: adenosine triphosphate; CPT: carnitine palmitoyltransferase; BNP: brain natriuretic peptide; CMR: cardiac magnetic resonance imaging; CS: coronary sinus; ECG: electrocardiogram; EF: ejection fraction; FAO: fatty acid oxidation; FWHM: frequency width at half maximum; HF: heart failure; ISIS: image selected in-vivo spectroscopy; jMRUI: java based magnetic resonance user interface; LV: left ventricle; LVSW: left ventricular stroke work; ME: mechanical efficiency; MRS: magnetic resonance spectroscopy; MLWHF: Minnesota Living with Heart Failure; NHYA: New York Heart Association; P-31: phosphorus-31; PCr: phosphocreatine; PV: pressure volume; RQ: respiratory quotient; SAE: serious adverse event; TCA: tricarboxylic acid cycle;
